In order to better understand reasons for refusal and survey attrition, to assess the usability of the IVR platform and receive feedback on the incentives and survey introductions, we will call a sub-sample of participants from *microtrials #1-5 and #7* and administer a short survey over the mobile phone. For each of these seven *microtrials*, we will call back a random sample of 30 individuals who did not complete the survey, 30 individuals who refused to consent to the survey, and 30 individuals who were identified as non-responders (i.e. did not initiate the survey); representing a total of 540 individuals in *microtrials* *#1-5, and 6,* per country.

**Fig 1**.Survey outcomes and number of participants who will complete a follow-up phone call

**
[figure not shown]
**

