The potential survey outcomes are depicted in figure 3. In a large proportion of the randomly selected mobile phone numbers, the randomly dialed mobile phone number may not exist, participants may refuse to participate in the MPS, or the mobile phone number may be valid, but the IVR survey was not initiated. Reasons for this latter category include, (1) phone was turned off or out of battery, (2) mobile phone was out of network coverage area, and (3) personal reasons, which include not hearing the mobile phone ring or respondent hanging up before consenting to the study. In these instances where the MPS was not initiated by a respondent, no future call back attempts to enroll participant will be made. Moreover, for respondents who initiate the IVR survey, but do not complete it (labeled an ‘incomplete survey’ in the figure), no call back attempts to re-initiate the survey will be made. Note, that as described in the sample size section, a sub-sample of participants (n=30) will be called back by a human interviewer to ask why they did not complete the survey. Unlike traditional household surveys, multiple attempts to achieve participant response are not needed since the selection of mobile phone numbers and timing of delivery are both random, thereby reducing the potential for non-response bias, but also because of the very large pool of possible respondents in the sampling set of all mobile phone owners.

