This microtrial seeks to examine whether the survey’s modality (IVR versus CATI) has a differential effect on the survey’s response and completion rates and to assess the ‘inter-modal reliability’. Participants will be randomized to one of two arms: 1) IVR then CATI or 2) CATI then IVR. Participants in the first study arm will receive an IVR survey first, followed by a CATI survey 7 days later. Participants in the second study arm will receive a CATI survey first followed by an IVR survey 7 days later. At initial enrollment, participants will be clearly explained that they are being enrolled in a microtrial where they will be contacted twice. The questionnaires used in both study arms will the same. This crossover design will allow for an assessment of response consistency, adjusted for the risk of ‘priming’ after exposure to the prior modality. This is the only *microtrial* that has participants answer two NCD surveys. The amount/timing/structure of incentive will be guided by the first three *microtrials*; where the incentive that yielded the highest response and completion rates will be provided to all participants in *microtrial* #7.

Follow-up of Non-response, Refusals, and Incomplete Interviews

For participants who were selected for the seven *microtrials,* a random sub-sample of participants who did not initiate the IVR survey, refused to participate, or partially completed an IVR survey, will be called back by a human operator using the same telephone number that was associated with the IVR. The study team will attempt to reach individuals up to three times. Unreached follow-ups will be documented. If successfully reached, the team will consent and interview participants to explore reasons for participant’s non-response, refusal, or incomplete surveys using a semi-structured guide (See Appendix 2). Demographic information from non-responders, refusals, and incomplete surveys will also be collected and examined in relation to the distribution of those who fully complete the survey.

**Table 2.** Study designs for Microtrials

|  | **Microtrial#1**  **Incentive Amount** | **Microtrial#2**  **Incentive Timing** | **Microtrial#3**  **Incentive Structure** | **Microtrial#4**  **IVR Intro features** | **Microtrial#5**  **IVR vs Human Intro** | **Microtrial#6**  **Sampling frame** | **Microtrial#7**  **Survey Modality** |
| --- | --- | --- | --- | --- | --- | --- | --- |

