***4. Provide a brief data analysis* plan *and a description of variables to be derived.***

The contact rates, response rates, and completion rates will be tabulated for each of the microtrials by study arm; where contact, response, and completion rates are defined as:

The contact, response, and completion proportions^[[1]](#footnote-1)^ will be tabulated for each of the *microtrials* and by study arm where contact, response, and completion are defined as:

$$Contact Rate= \frac{CI+PI+R}{CI+PI+R+(NC+U)}$$

$$Response Rate= \frac{CI+PI}{CI+PI+R+NC}$$

$$Completion rate= \frac{\mathrm{CI}}{CI+PI+R}$$

**CI** (Complete Interview): a respondent that answered all applicable questions

**PI** (Partial interview): a respondent who consented to the survey but did not answer all questions

**R** (Refusal): a respondent who: 1) did not consent to the survey, or 2) formally withdrew during the survey

**NC** (Non-contact): a working phone number where the respondent picked up but did not engage with the survey. This is assessed by looking at the system log for time spent on the survey

**U** (Unknown): a phone number that cannot be determined whether it is a working phone number (the respondent did not pick up the phone) or not (the phone number is not eligible)

Respondents who report being less than 18 years old are considered ineligible. Ineligible respondents are excluded from the equations for contact, response, and completion rates.

Contact, response, and completion proportions will be compared by study arm for each microtrial and by incentive group. *A priori, a*n alpha of 0.05 will be used for hypothesis testing.

Partially completed surveys will be tabulated and stratified by both the question number, and the question content due to the randomization of NCD topic modules. Additionally, the average time spent answering, the number of “Don’t know” or “Refuse to answer” responses, and the number of times the question was repeated will be calculated for both the chronological question number and question content and stratified by study arm. For microtrial #7, test for agreement in survey responses between the survey modalities will be assessed using Cohen’s Kappa.

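### In microtrial 2 the response and completion rates are conditional on pick-up, which prepaid airtime can change, yet the incentive carried forward is chosen on those two rates

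*Protocol*

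**What the plan says.** Section V.C.4 of the protocol defines three rates:

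- Contact = (CI+PI+R)/(CI+PI+R+NC+U)
- Response = (CI+PI)/(CI+PI+R+NC)
- Completion = CI/(CI+PI+R)

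U is "a phone number that cannot be determined whether it is a working phone number (the respondent did not pick up the phone) or not". NC is "a working phone number where the respondent picked up but did not engage with the survey". So U counts in full in the contact rate and not at all in the other two. All three rates are to be compared by arm.

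Elsewhere the protocol takes a wider view of non-response. The sample size section (III.B) plans call-backs to "30 individuals who were identified as non-responders (i.e. did not initiate the survey". Survey Delivery (V.C.1) describes a group where "the mobile phone number may be valid, but the IVR survey was not initiated". Its reasons include "phone was turned off or out of battery", being out of coverage, and "not hearing the mobile phone ring or respondent hanging up before consenting to the study".

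Microtrial #2 (V.C.1) randomises to no incentive, a part-prepaid incentive, or an incentive promised on completion. The prepaid part is sent after the notification SMS and before the survey starts. The stated aim includes an effect on contact. For microtrial #7, "the incentive that yielded the highest response and completion rates will be provided to all participants". Microtrial #6 likewise takes the top-performing incentive from microtrials 1 to 3.

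**The concern.** Randomisation makes the arms comparable over all numbers assigned to them. It does not make those who answer comparable if the arm affects answering. In microtrial 2 it may: airtime arrives before the phone rings, and the protocol itself asks whether timing alters contact. A rate restricted to answerers then mixes two effects, a change in willingness and a change in who is being asked.

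The two rates in the microtrial 7 selection rule both have this restriction, and completion also leaves out NC. If prepaid airtime brings in extra answerers who are less willing than the usual ones, it lowers both rates while raising the number of respondents and completes. The rule as written would then discard the more productive incentive. The reported finding of microtrial 2 on response would point the same wrong way.

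**Working it through.** **Plan's own figure.** The protocol states no pick-up or response figure to reproduce. Its one related figure is the sample size. For 30% against 40% completion, two-sided alpha 0.05 and 80% power, the formula gives 356 per arm, or 376 with continuity correction; 376/0.30 rounds up to 1,254. This matches section III.B and is not in dispute.

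**Condition for a reversal.** Let N be the numbers randomised per arm (equal in both arms), A = CI+PI+R+NC the pick-ups, and k the ratio of pick-ups, prepaid to promised. Respondents per number = response rate × A/N. So the ratio of respondents per number = (ratio of response rates) × k. The response rate ranks prepaid lower while prepaid yields more respondents exactly when

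1/k < (prepaid response rate / promised response rate) < 1.

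**Example 1 (assumed counts, N = 10,000 per arm).** Promised: 2,000 pick up, 600 respond. Prepaid: 2,500 pick up, and the extra 500 respond at 15%, giving 600 + 75 = 675.

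- Response as defined: 600/2,000 = 30.0% against 675/2,500 = 27.0%; pooled z = -2.22, prepaid worse.
- Per number: 600/10,000 = 6.0% against 675/10,000 = 6.75%; z = +2.17, prepaid better.
- Condition: k = 1.25, 1/k = 0.80, ratio of rates 0.90, which lies between 0.80 and 1.

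**Example 2 (assumed, all dispositions, N = 10,000 per arm).** Promised: CI 600, PI 400, R 500, NC 500, U 8,000. Prepaid: CI 720, PI 480, R 840, NC 960, U 7,000.

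| Measure | Promised | Prepaid | Ranked first |
| --- | --- | --- | --- |
| Response | 1,000/2,000 = 50.0% | 1,200/3,000 = 40.0% | Promised |
| Completion | 600/1,500 = 40.0% | 720/2,040 = 35.3% | Promised |
| Contact | 1,500/10,000 = 15.0% | 2,040/10,000 = 20.4% | Prepaid |
| Respondents per number | 10.0% | 12.0% | Prepaid |
| Completes per number | 6.0% | 7.2% | Prepaid |

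Both rates in the selection rule point one way and both yields point the other.

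**How far this depends on the assumptions.** Take half of numbers working, 30% base pick-up, k = 1.25, and 50% response among usual answerers. The promised arm then has a response rate of 50% and 7.5% respondents per number. The prepaid arm gives:

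| Response among extra answerers | Response rate | Respondents per number | Ranking reversed? |
| --- | --- | --- | --- |
| 10% | 42% | 7.9% | Yes |
| 30% | 46% | 8.6% | Yes |
| 50% | 50% | 9.4% | No |
| 70% | 54% | 10.1% | No |

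With working shares from 25% to 75% and k of 1.1, 1.25 or 1.5, the pattern was the same: reversal at 10% and 30%, none at 50% and 70%. What decides it is whether the extra answerers are less willing than the usual ones.

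**The case against.** The strongest reply is that the plan does not read response alone. Contact is compared by arm too, and contact × completion = CI/(CI+PI+R+NC+U), which is completes per number. In example 2, 15.0% × 40.0% = 6.0% and 20.4% × 35.3% = 7.2%, the correct ranking. This stands as far as it goes: an attentive analyst could recover the yield of completes. Two gaps remain. Respondents per number cannot in general be recovered from the three rates, because the contact numerator omits NC. And the microtrial 7 rule names response and completion only.

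A second reply is that conditioning on pick-up is harmless where the arm cannot affect it, and helps precision. This also stands. The SMS is described as giving purpose, time and sponsor, and incentives are announced in the introduction. In microtrials 1, 3 and 4 the documents show no route from arm to pick-up. A reader might infer that the response rate should be replaced throughout; the documents do not support that.

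Three other stronger readings also fail:

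- A reader might say that the response rate drops all of the protocol's non-responders. People who answer but do not engage are NC and stay in its denominator; only those who never answer leave it.
- A reader might infer that dead numbers make up most of U. Survey Delivery says "the randomly dialed mobile phone number may not exist", but the large proportion it mentions covers non-existent numbers, refusals and valid numbers with no survey started, taken together. No separate share is given.
- A reader might extend the point to microtrial 6, on the ground that an operator's list holds few dead numbers. The documents do not say so.

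**Conclusion.** The concern holds for microtrial 2 and for the choice of incentive that draws on it. The response and completion rates are conditional on a step that prepaid airtime can change, and the selection rule uses only those two. Followed as written, it can pick the less productive incentive.

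The size cannot be fixed from the documents, which give neither a pick-up rate nor a share of working numbers. The 30.0% against 27.0%, turning into 6.0% against 6.75%, is an illustration. A reversal needs prepaid airtime to raise pick-up and the added answerers to be sufficiently less willing; otherwise the rates and the yields agree. The counts also assume that every randomised number is called. Survey Delivery hints at an SMS reply requirement in microtrial 2 that the description of that microtrial does not explain.

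The consequence is limited. All participants in microtrial 7 receive the same incentive, so a poor choice costs efficiency and does not bias IVR against CATI. Microtrial 3 takes only the amount from microtrial 1 and pays its fixed arm after completion, so it is untouched. The sample size of 376 is unaffected.

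**What to change.** Keep the three rates of section V.C.4 as descriptive outcomes. For microtrial 2, add two comparisons by randomised arm: respondents, (CI+PI)/(CI+PI+R+NC+U), and completes, CI/(CI+PI+R+NC+U). Treat those who report being under 18 in the same way in each arm, and state which way. Note that completes per number equals contact × completion. Dead numbers should balance between randomised arms, so no estimate of the working share is needed.

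In the microtrial 6 and 7 descriptions, base the incentive choice on these two yields wherever incentive timing is involved. In section V.C.4, state that the response rate is conditional on pick-up and so excludes non-responders who never answer.

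The cost is wording only, since counts of U by arm are already needed for the contact rate. The added percentages will look low, and some precision is lost if pick-up does not differ. For example, 600 against 800 respondents gives z = 6.6 over 2,000 answered per arm and z = 5.5 over 10,000 dialled.

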**VI. Data Custody, Security, and Confidentiality Protections**

*The sections below describe types of data sources and how they will be protected. For the type(s) of data you will have, put an “X” in the appropriate box to the left of the section that best describes how you will minimize the risk of a breach of confidentiality for your study. Note, as appropriate, how you will record/store data. These descriptions represent MINIMAL measures; you may add more stringent protections and other relevant information in B*.

**Confidentiality: The *LOSS OR THEFT* of 1) original/duplicate version of physical data collection instruments (forms, tapes, etc) or 2) physical devices containing electronic data (i.e. laptop/mobile device, external flash drive(s), is a threat to subject confidentiality. Risk of such a loss/theft is increased during movement/transport of data (in any format), such as in a vehicle or other move. Be sure to train anyone (co-investigators, staff, students, etc.) who might be engaged in the oversight of data handling/storage about this problem. Some typical risk-mitigation strategies would include:**

- **minimizing the physical movement of data and/or devices containing data**
- **encrypting electronic data (especially when stored on any mobile device, including flash memory tools, phones, tablets, etc, or when transferring across networks)**
- **making use of reliable courier services (FedEx, DHL, etc) when physical transport of bulk data forms is necessary**
- **minimizing the transfer of identifiable data in physical or electronic form (i.e. removing/separating/destroying identifiable data, when physical transfer of data is necessary)**

A. Data Storage

| 1. Hard Copies of Data Collection Forms. | |
| --- | --- |
| X | This activity will not involve receiving and/or accessing hard copies of data |
|  | Data collection forms RECORD NO PERSONAL IDENTIFIERS connecting study participants, and there are no codes providing a link. Data are anonymous. |
|  | Data collection forms INCLUDE IDENTIFIERS. The forms are locked in a secure cabinet or room with limited access by authorized individuals. Forms will be kept in study team’s possession during transport and will not be left unattended in a vehicle. When possible, de-identified copies will be used for coding and analysis. |
|  | Data collection forms ARE CODED with study participants’ random study ID numbers. Codes/links between study IDs and identifiers are stored securely in a separate place (locked storage cabinet or secure electronic database.) |
|  | Other: |
| 2. Electronic Data | |
|  | The data do not contain personally identifiable information |
|  | These data are stored on a secure server protected by limited access and strong password systems. Data are coded when possible. Portable electronic devices will not contain identifiable information unless encrypted. |
| X | Other: Phone numbers will be logged in a security encrypted and password protected VOTOmobile platform alongside other non-identifiable data. Immediately after each microtrial has been completed, the PI will download the database from the VOTOmobile platform and permanently delete the column containing mobile phone numbers. |
| 3. Other Identifiable Data Storage, Retention, and Destruction (Audiotapes, videotapes, photographs, etc.) will be retained and stored securely (locked in cabinet or room) until: **NA** | |
|  | Transcription is complete, then will be destroyed. |
|  | Analysis is complete, then will be destroyed. |
|  | Study is complete and file is closed. |
|  | Indefinitely. Provide justification for indefinite retention: |
| 4. Existing Biospecimens to be used in this study: **N/A** | |
|  | HAVE NO PERSONAL IDENTIFIERS. |
|  | INCLUDE IDENTIFIERS AND ARE CODED; the PI will not have access to the link or code connecting the identifiers to the specimens. |
|  | INCLUDE IDENTIFIERS, and the PI has access to those identifiers or to the link/code connecting specimens to individuals. The identifiers and/or code will be stored securely until the study is complete. |

B. **Certificate of Confidentiality**

***Will the study data stored in the United States be protected by a Certificate of Confidentiality? If yes, explain who will apply for and maintain the Certificate.*** (<http://grants.nih.gov/grants/policy/coc/appl_extramural.htm>)

No

C. **Data Security and Sharing**

***PIs have the responsibility for responsible stewardship of data and protecting data confidentiality. This responsibility includes protecting physical custody of the data, storage and sharing with appropriate data use agreements that contain the appropriate security provisions. Describe any additional plans beyond those identified in the table that you have for storing and sharing the study data and/or materials, and how responsibility for the data will be managed. Include the following details:***

*1.* ***Where will the study data be stored?***

*2.* ***Who controls access to the data?***

*3.* ***Will data be shared only if de-identified?***

*4.* ***What additional (if any) security controls will be in place*?**

Electronic data (survey results) will be downloaded from VOTOmobile’s cloud platform onto a password protected computer of the study staff, located behind a locked door at JHSPH. As above, these data will permanently de-identified by stripped them of phone numbers. Only members of the JHSPH study team will have access to these data. Data shared with partner countries will also be de-identified and maintained in locked filing cabinets and on password protected computers. Country investigators will follow data security protocols of their home institutions.

**VII. Risks of the Study**

***A. Describe the risks, discomforts, and inconveniences associated with the study and its procedures, including physical, psychological, emotional, social, legal, or economic risks, and the risk of a breach of confidentiality. These risks should be described in the consent documents.***

There are no foreseeable physical risks to study participants. During the IVR survey, some participants may feel uncomfortable or bored while answering questions. Minor psychological discomfort may be associated with responding to questions of a personal nature on habits regarding socially undesirable behaviors such as use of tobacco products, alcohol, or unhealthy diet and physical inactivity.

A limited number of questions will be asked of individuals to minimize inconvenience and boredom. The survey is expected to last no longer than 30 minutes. To minimize risks of psychological discomfort, participants will be informed that they do not need to answer any question that they feel uncomfortable with and that their participation in the survey is voluntary. As the IVR survey will collect responses from individuals non-verbally (i.e., by pressing numbers that correspond with answer choices), the likelihood of responses being known to others who may be in their vicinity is also decreased.

*B.* ***Describe the anticipated frequency and severity of the harms associated with the risks identified above; for example, if you are performing “x” test/assessment, or dispensing “y” drug, how often do you expect an “anticipated” adverse reaction to occur in a study participant, and how severe do you expect that reaction to be?***

We do not know precisely the frequency and severity of potential discomfort but anticipate that it will be quite infrequent and minimal given the nature of the survey questions.

*C.* ***Describe steps to be taken to minimize risks. Include a description of your efforts to arrange for care or referral for participants who may need it.***

To minimize risks associated with answering questionnaires, participants will be informed that they do not need to answer any question that they feel uncomfortable with and that their participation in the IVR survey is voluntary. Participants will be informed and allowed to end their participation at any time. To minimize risk of confidentiality breach, we have employed several safeguards. First, the IVR survey does not collect any personal identifying information aside from the mobile phone number (date of birth and name are not collected). Following completion of the IVR surveys, the PI will download data from the VOTOmobile platform and permanently delete the column containing mobile phone numbers. After this step, there will be no record of mobile phone numbers associated with the IVR survey.

No names will be used in any reports or documents stemming from this research protocol. Study staff who are involved with microtrial 5 and microtrial 7 (human operators) and who call back participants to understand reasons for their non-participation will be trained in human research ethics.

*D.* ***Describe the research burden for participants, including time, inconvenience, out-of pocket costs, etc.***

Overall, participants will spend up to 30 minutes for each mobile phone survey in the seven microtrials. For microtrial seven, participants receive two mobile phone surveys. This amount of time may be inconvenient for participants. In a sub sample of microtrial participants, we will call individuals to understand reasons for their non-participation; at most, this would be 30 minutes. The costs of airtime associated with answering the MPS will be borne by the study team and transferred directly to respondents within 24 hours of their completing a survey. VOTOmobile has experience with issuing airtime credit transfers across multiple mobile network providers. Therefore, participants will not incur any out-of-pocket expenses as part of their participation in the study.

*E.* ***Describe how participant privacy will be protected during data collection if sensitive questions are included in interviews.***

The survey questions are administered over a telephone call. Therefore, it will be difficult for people not associated with the study to hear and understand the survey questions and participant’s responses.

